#### Statistical analysis

All data analysis will be conducted by the basic principles of Intentional Analysis (ITT), including data on any participants who withdrew from RCT during the trial (26). The statistical analysis of the data will be carried out using SPSS26.0 software. The data files will be locked after blind review and determined to be reliable and correct, and the whole process of analysis will be unblinded twice.

The full analysis protocol set will be selected for demographic and other baseline characteristics analysis. To evaluate the therapeutic effect and safety, FAS and PPS will be used at the same time. For the efficacy index, endpoint, and outcome index, the intention analysis will be mainly used for the full analysis set (FAS), and the compliance scheme set (PPS) will be analyzed to compare the results of the two data sets; If not, find the reason. After randomization, statisticians will perform safety data set analysis on subjects who received at least one treatment.

This study is a multi-center clinical trial. CMH method was used for counting data, and analysis of variance and analysis of covariance were used for measurement data.

According to factors such as age, gender, history of insomnia, school, etc., a subgroup analysis will be performed to evaluate the difference in intervention efficacy among different populations.

All statistical analysis will be performed in SPSS 26.0 software, *p* < 0.05 will be considered statistically significant, and statistical analysis and supervision will be carried out by statistical experts who do not understand the experimental scheme and group assignment.

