**Methods and analysis:**

This is a multicenter, single-blind, randomized controlled trial. A total of 126 eligible subjects who have passed the psychological evaluation and met inclusion criteria by completing a psychometric scale will be randomly divided into treatment group A (treat before sleep), treatment group B (treat after sleep) and control group C (waiting list group) in a ratio of 1:1:1. All the three groups will receive regular psychological counseling during the trial, and the treatment groups will practice 24-style Taijiquan and do meridian acupuncture at Baihui (DU20), Shenting (DU24), Yintang (EX-HN3), Shenmen (HT7) and Sanyinjiao (SP6). This RCT includes a 2-week baseline period, a 12-week intervention period, and a 12-week follow-up period. The main results will be measured by changes in the Pittsburgh sleep quality index (PSQI) and Hamilton anxiety scale (HAMA). The secondary results will be measured by the generalized anxiety scale (GAD-7) and insomnia severity index (ISI). The safety of the intervention will be evaluated at each assessment. The statistical analysis of data will be carried out by SPSSV.26.0 software.

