Natural, focused awareness appropriate speed and outstanding style	1–3 marks will be deducted for minor deviations from the requirements, 4–6 marks for significant deviations and 7–10 marks for serious deviations.
Forgetting the action	3–5 marks will be deducted for each instance of forgetfulness, depending on the degree.
Out of balance	1 point for each wobble; 2 points for each support; 3 points for successive supports.
Number of movements	3 marks will be deducted for each extra or missing movement.
Direction of movement	One point for each deviation of 45° or more from the prescribed direction.
Repeat the set	If the examination is interrupted due to forgetfulness or mistakes, the examination may be repealed once and 10 points deducted, and so on.
Unfinished sets	Those who do not complete the routine will not be graded and will be marked as failing.

A total of 100 points will be awarded, with a total score of less than 60 being unqualified.

Group A receives combined treatment 30 min before sleep. First, 24-style Taijiquan training will be performed for 15 min each time, once a day. Then do acupoint pressing at Baihui (DU20), Shenting (DU24), Yintang (EX-HN3), Shenmen (HT7), and Sanyinjiao (SP6), kneading 1∼2 times for 1∼2 min. And then replacing with the next acupoint, each acupoint will be kneaded 1∼2 back and forth, a total of 15 min of continuous pressing. After each treatment, study members should make strict records to ensure the full participation of subjects in the study (18). Group B does the therapy of Taijiquan combined with acupoint pressing 30 min after waking up, and the treatment procedures and methods are the same as those of Group A. Group C will not accept any intervention on Taijiquan or acupoint pressing, and maintain their normal lifestyle. After the study, subjects in this group can choose to participate in the treatment of 24-style Taijiquan training combined with acupoint massage.

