#### Safety evaluation

In the process of this research, researchers should monitor and record the adverse events or emotional reactions of subjects, and analyze the causal relationship between the combination treatment and the severity of the adverse events in time (23). During the trial, any adverse events (defined as falls, sprains, any sports-related injuries, etc.) will be recorded. If an adverse event occurs, and the subject has emotions such as mania, severe depression, extreme depression, etc. The experiment should be terminated in time, and psychological counseling or medication should be immediately accepted.

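### Three unranked populations are named for safety: one leaves out the waiting-list arm, one can drop those who stopped because of harm, and the adverse event definition is built around exercise injuries.

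*Protocol article*

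**What the plan says.** All references are to the protocol article.

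- **Populations for safety (Statistical analysis).** Two sets are named together: "To evaluate the therapeutic effect and safety, FAS and PPS will be used at the same time". The same paragraph then adds a third: "statisticians will perform safety data set analysis on subjects who received at least one treatment". It makes the FAS the main set for the efficacy and outcome measures, but gives no such order for safety. The section opens by placing all analysis on the intention-to-treat principle, with the data of withdrawn participants included.
- **What group C receives (Interventions).** "Group C will not accept any intervention on Taijiquan or acupoint pressing, and maintain their normal lifestyle". Access comes later: "After the study, subjects in this group can choose to participate in the treatment of 24-style Taijiquan training combined with acupoint massage".
- **Co-intervention (abstract, Methods and analysis).** "All the three groups will receive regular psychological counseling during the trial".
- **Adverse events (Safety evaluation).** "any adverse events (defined as falls, sprains, any sports-related injuries, etc.) will be recorded". The same section has researchers record emotional reactions of subjects alongside adverse events, with no arm excluded, and asks for an analysis of the causal link to the combined treatment.

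**The concern.** The Discussion gives efficacy and safety together as the aim of the trial. Because the Safety evaluation section asks for a causal assessment, a comparator matters: the Discussion expects most participants to tend toward anxiety and depression, so mood and sleep complaints will arise in every arm. A safety set holding only groups A and B can give an absolute event rate but cannot separate treatment from that background.

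A PPS raises a different problem. If membership depends on completing the treatment, people who stopped because of an event may be removed from the analysis meant to count them.

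With three sets and no order among them, the report can show up to three denominators and three rates, and nothing says beforehand which one is the trial's safety result. A definition whose named examples are all injuries of physical activity adds an imbalance in what is likely to be asked about and written down in each arm.

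**Working it through.** **Inputs.** Total 126, allocation 1:1:1 (abstract; Study design). α = 0.05 two-sided, power 0.90, rates 0.68 and 0.92, pooled 0.80, expansion 10% (Sample size).

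**1. The plan's own total.** The safety rules carry no figure, so the only stated number to reproduce is the sample size. With the usual two-proportion formula, variance terms added:

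n per arm = [1.960·√(2·0.80·0.20) + 1.282·√(0.68·0.32 + 0.92·0.08)]² / (0.92 − 0.68)²
= [1.109 + 0.692]² / 0.0576 ≈ 56.3, rounded up to 57.

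2 × 57 = 114, and 114 × 1.10 = 125.4, rounded up to 126. The total is reproduced and serves here only as the denominator. (That 114 is a two-arm total is a separate matter.)

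**2. Who falls in each set.** 126 / 3 = 42 per arm.

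| Set named for safety | Group A | Group B | Group C | Total |
|---|---|---|---|---|
| Safety set, treatment = Taijiquan or pressing | up to 42 | up to 42 | 0 | up to 84 |
| Safety set, if counseling counts as treatment | up to 42 | up to 42 | up to 42 | up to 126 |
| FAS, read as intention-to-treat | up to 42 | up to 42 | up to 42 | up to 126 |
| PPS | compliers only | compliers only | not stated | not stated |

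On the first reading 42/126 = 33.3% are left out, all of them controls. With no events among 84, the one-sided 95% upper limit for the event rate is 1 − 0.05^(1/84) = 3.5%. The set can give an absolute bound of that kind, but no difference between arms.

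**3. Which reading of treatment is the natural one.** The article keeps the label of treatment groups for A and B, and describes group C as able to choose the treatment only after the study. That supports the first row. The second row is possible, but the text does not state it.

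**4. What the PPS can do to a rate.** The article gives no events and no PPS criteria, so this is an assumed illustration. Let 4 of 42 in one active arm have an event, and let k of those 4 stop and be excluded. The PPS rate is (4 − k)/(42 − k):

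| k | PPS rate |
|---|---|
| 0 | 4/42 = 9.5% |
| 1 | 3/41 = 7.3% |
| 2 | 2/40 = 5.0% |
| 3 | 1/39 = 2.6% |
| 4 | 0/38 = 0% |

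The rate falls only when exclusion is linked to the event. If 4 people without an event were excluded instead, it would be 4/38 = 10.5%. In every case all 4 remain in the FAS and, having had a session, in the safety set.

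**5. The definition against the intervention.** Every named example is an injury from movement. Half of each 30-minute session is acupoint pressing, and the Interventions section asks for pressure felt as pain, yet no harm of pressing is named. Emotional reactions stand beside adverse events rather than within them, so it is unclear whether they enter an adverse event rate.

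**The case against.** The strongest reply is that the plan as a whole already protects the safety comparison. The FAS is named for safety, withdrawals are kept under intention-to-treat, and case report forms collect adverse events for participants without limiting this to an arm. This stands, and it rules out three stronger readings that a reader might infer:

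- **That the trial would have no comparative adverse event rate.** Controls are missing from one set. The FAS can supply the comparison.
- **That those who stop treatment are shut out.** Anyone with a single session stays in the safety set, and the FAS should keep them too. Only the PPS run can lose them.
- **That worsening mood or sleep is left to the open ending of the definition.** Emotional reactions are recorded separately, and sleep and anxiety are measured by PSQI, ISI, HAMA and GAD-7 in all arms. Falls and sprains can also happen to controls, so the definition is tilted toward the exercising arms rather than confined to them.

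It can also be said that requiring one treatment is standard wording, that counseling might count as treatment, and that a condensed article leaves set membership to the analysis plan. The point about counseling stands as an uncertainty. The last point does not remove the concern: the article itself states the three rules, and they give different denominators without an order.

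**Conclusion.** The point holds as a conflict among stated rules, not as a failure of the whole safety plan. On the plain reading the safety set excludes all 42 of group C (33.3% of 126) and has no comparator. The PPS is a poor safety population, because a rate from it is too low whenever exclusion follows from harm. No set is named as the main one for safety. The adverse event definition leans toward exercise injury and does not name harms of pressing.

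This rests on three assumptions: that treatment means Taijiquan or pressing, that the FAS follows intention-to-treat and so holds the controls (the article does not define it further), and that the planned 126 are split equally. The size of the PPS distortion is unknown; 9.5% falling to 0% is the extreme of an assumed example. The FAS should not be read as a defective safety set, since it is the one named set that, on these assumptions, keeps both controls and withdrawals. The sponsor should correct this; the primary efficacy analysis is not affected.

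**What to change.** 1. Name one safety population of all randomised participants. Groups A and B are analysed by the condition received (at least one session), and group C is included as the waiting-list comparator. State where someone allocated to A or B who never starts a session is counted, and that counseling alone does not decide membership.
2. Remove the PPS as a safety population. It can stay as a supporting set for efficacy.
3. Define an adverse event as any untoward event in any arm, with exercise injuries and harms of acupoint pressing as subcategories, and say whether recorded emotional reactions count.
4. Ask about adverse events with the same question in all three arms at the existing assessments.

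The cost is protocol wording and one uniform question on the case report form. No visit is added and no treatment changes.

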#### Patient and public involvement

Patients or the public were not involved in the design, conduct, reporting, or dissemination plans of this research.

#### Ethics and dissemination

This research project was examined and approved by the Ethics Review Committee of the Hospital of Chengdu University of Traditional Chinese Medicine in January 2022 (approval number: 2022KL-004). Before the pilot study, all participants will sign a written informed consent form. The results will be disseminated through peer-reviewed publications or conference reports. The data will be anonymous before publication to prevent the identification of individual participants.

## Discussion

This trial is a randomized controlled clinical trial, which aims to evaluate the efficacy and safety of Taijiquan combined with acupoint pressing in the treatment of anxiety insomnia in college students and to determine the best intervention time for Taijiquan combined with acupoint pressing in the treatment of anxiety insomnia.

Studies have shown that practicing Taijiquan and acupoint pressing can reduce the symptoms of anxiety insomnia to some extent, but the effectiveness of the combination of Taijiquan and acupoint pressing in the treatment of anxiety insomnia is not clear (27, 28). This experiment will be conducted in multiple centers, using a randomized controlled trial to blind the trial evaluators and data statistical analysts to evaluate the effectiveness of Taijiquan combined with acupoint pressing in the treatment of anxiety insomnia in college students. By comparing different treatment times of Taijiquan and acupoint pressing, we can find the best time for the treatment of anxiety insomnia. In addition, this study designed according to the Comprehensive reporting Test Standard (CONSORT) statement and guidelines will provide effective evidence for guiding the clinical practice of Taijiquan combined with acupoint pressing in the treatment of anxiety insomnia.

Our research has the following advantages. First of all, to ensure the quality of the study and reduce the influence of confounding factors, the research team will conduct a baseline assessment of the subjects. The subjective evaluation results will be obtained by using PSQI, HAMA, Generalized anxiety scale (GAD-7), and Insomnia Severity Index (ISI). The emotional changes of the subjects during the experiment will be recorded objectively by the study members (29). Through the analysis of a large number of papers, Baihui, Sanyinjiao, Shenmen, Yintang, and Shenting are recognized as acupoints with good curative effects in the treatment of insomnia (30–32). This experiment does not use skin-breaking intervention, but self-acupoint pressing intervention to ensure the safety and controllability of the trial to a certain extent, and increase the feasibility of the trial. Secondly, the subjectivity of the subjects in this experiment is strong. To ensure the validity of the experimental research data and reduce the deviation caused by the amount of operation or non-standard operation, senior acupuncture and massage lecturers and Taijiquan professional teachers are arranged to conduct regular acupoint pressing and Taijiquan training for the subjects so that the subjects can carry out the standard operation in the prescribed treatment period. In addition, most of the subjects in this experiment have a certain tendency toward anxiety and depression. To maintain the physical and mental health of the subjects and ensure that the subjects could complete the research experiment, the research team specially equipped professional psychological counselors to carry out regular psychological counseling, and the researchers recorded their emotions to prevent overreaction in the research process. In the course of the experiment, the research team will collect the subjective scale data and objective emotional records of the subjects every 3 weeks, and analyze the effectiveness and difference of Taijiquan combined with acupoint pressing therapy in treatment groups and control group (33, 34). After 12 weeks of intervention, all participants will begin an unsupervised follow-up period of another 12 weeks to restore their daily lifestyle and re-use the results of the scale to analyze the long-term effect of combined therapy. In Chinese clinical research trials, the effects of Taijiquan and acupoint pressing in the treatment of insomnia will vary with different intervention times, so the intervention time in this experiment is also the expansion angle of the combined therapy, which will also be the focus of this study report.

This study has certain limitations. The research team cannot use the blind method for the test subjects, so the test process adopts the random distribution sequence results. The test treatment period and grouping process are confidential to the subjects, and the evaluators and data statistical analysts are blinded (35). The random distribution information cannot be disclosed until the research and test are completely completed. At the same time, subjects are not allowed to communicate treatment measures with each other during the trial, so as not to increase the influence of confounding factors.

This experimental study will collect experimental data from subjective and objective to analyze the effectiveness of Taijiquan combined with acupoint pressing in the treatment of anxiety insomnia of college students. It is of great significance for clinical practice to find the best time for the treatment of anxiety insomnia in college students (36). The results of the follow-up data of subjects are also expected to evaluate the effectiveness of Taijiquan combined with acupoint pressing as adjuvant therapy or preventive intervention of specific health status in the treatment of clinical anxiety insomnia.

## Ethics statement

This experiment has been approved by the Medical Ethics Committee of the Hospital of Chengdu University of Traditional Chinese Medicine, and the ethical approval mark is 2022KL-004.

## Abbreviations

PSQI: Pittsburgh sleep quality index
HAMA: Hamilton Anxiety Scale
GAD-7: Generalized Anxiety Disorder
ISI: Insomnia Severity Index.
